### Ethical Considerations

The approval for the protocol of this study was granted by the Health Ethics Committee of the Centro de Medicina de Reabilitação da Região Centro–Rovisco Pais (Tocha, Portugal) in August 2022.

### Consent to Participate and Consent for Publication

#### Overview

A document was developed at the request of the health ethics committee for informed, clear, and voluntary consent for participation in research studies. The document outlines the research study’s objective and assures that there will be no detriment to treatments and clinical follow-up should the patient choose to withdraw. It also guarantees the anonymity and confidentiality of all collected data, including photographs, results from the Quebec User Evaluation of Satisfaction With Assistive Technology (QUEST) [18], and biomechanical analysis data. The consent form must be signed by both the attending physician and the patient.

This protocol was prepared according to the SPIRIT (Standard Protocol Items: Recommendations for Interventional Trials) 2013 checklist for reporting a protocol study [19].

#### Eligibility Criteria and Recruitment Procedures

The inclusion criteria for this study have been defined with precision to select the most suitable candidates in alignment with the study objectives. We are targeting survivors of stroke, both male and female, aged between 18 and 75 years, who exhibit equinovarus foot secondary to hemiparesis, affecting either the left or right side. A prerequisite for potential participants is their current use of AFOs. Furthermore, the concurrent use of any assistive technologies such as tripods, crutches, or canes is deemed acceptable. Essential criteria include the capacity to provide informed consent and the ability to ambulate, either independently or with the support of the aforementioned devices. Conversely, candidates with concomitant neurological or orthopedic conditions that might confound the study outcomes, those with active dermatological conditions, or those with severe communication impairments potentially hindering consistent participation will be excluded.

The recruitment process will be at the Centro de Medicina de Reabilitação da Região Centro. Attending physicians will review patient profiles to identify individuals meeting the stipulated criteria. Those aligning with our research parameters will be briefed on the study’s aims and subsequently provided with a detailed consent document. Upon granting written consent, these individuals will be enlisted as participants, ensuring a systematic and ethically rigorous approach to data acquisition and feedback.

#### Clinical Outcomes

In the pursuit of developing an optimized orthotic design system, an array of clinical metrics is implemented to gauge its efficiency, efficacy, and the comfort it bestows on both patients and health care professionals. Ensuring a comfortable experience for the patient during the photography process is paramount, given its pivotal role in orthotic design. This precision not only benefits the patient but also ensures that the system health care professionals navigate is intuitive.

Biomechanical assessments use the Qualisys Miqus M3 system, paired with Bertec force platforms. Patients will wear the Calibrated Anatomical System Technique lower body marker set, which consists of 36 reflective markers, as prescribed by Cappozzo et al [20]. Observations cover 3 walking conditions for each participant: unaided (where possible), with the current orthosis, and with the newly designed orthosis. This methodology provides an in-depth understanding of the orthosis’s efficacy, drawing from 10 walking cycles for each leg, and analyzing both kinematics and kinetics.

The biomechanical data under scrutiny spans temporal-spatial parameters, which capture walking speed, gait cycle duration, step length, step time, time in stance, and time in swing. Kinematic parameters delve into pelvic movements such as anterior tilt, up obliquity, and internal rotation. Hip parameters include flexion, adduction, and internal rotation, while knee parameters assess flexion, varus, and internal rotation. Ankle and foot evaluations note dorsiflexion, inversion, pitch, and internal progression. Kinetic parameters are marked by the internal moments at the hip (extensor and valgus), knee (extensor and valgus), and ankle (plantarflexor and extensor), accompanied by the vertical ground reaction force.

The qualitative patient analysis will also incorporate the QUEST assessment. QUEST focuses on understanding the user’s satisfaction with assistive technology. It evaluates a range of aspects, from device functionality to user confidence. This offers insights into patients’ perceptions and benefits derived from the new orthosis in comparison to conventional models. Incorporating QUEST ensures the orthosis not only meets clinical requirements but also aligns with patient preferences and comfort levels.

Through these comprehensive evaluations, the study aims to offer an enriched perspective on the potential and effectiveness of the innovative orthotic system.

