### Data Analysis

The forthcoming data analysis is designed to provide an in-depth understanding of the impact of personalized orthoses on gait parameters in relation to both preexisting orthosis and barefoot walking. The sample size was estimated at a prespecified power of 90%, while the α value was set at <.05. The primary outcomes will be represented through spatial-temporal data tables and normalized gait graphs, spanning from 0% to 100% of the gait cycle for the left and right legs.

Spatial-temporal parameters will undergo statistical comparisons using paired *t* tests. This will discern any significant differences between walking with the personalized orthosis, the preexisting orthosis, and walking barefoot. Significant distinctions will be recognized based on *P* values, with a threshold set at 95% indicating statistical significance.

Graphical comparisons of kinematic and kinetic data will use the Statistical Parametric Mapping (SPM) method. SPM is tailored for the analysis of 1D biomechanical data series, such as kinematic curves, yielding a nuanced understanding of differences across the entire gait cycle rather than mere isolated time points. The analysis will leverage the *SPM1D* script. By using SPM1D, it becomes feasible to pinpoint regions in the gait cycle where palpable differences between conditions (existing orthosis, personalized orthosis, and barefoot) arise. This rigorous method offers a continuous evaluation over the entire time or space continuum, safeguarding against missing subtle yet clinically pivotal variations.

Simultaneously, the QUEST responses will be statistically analyzed to evaluate patient satisfaction. Scores from the QUEST, which range from 1 (not satisfied) to 5 (very satisfied), will be presented as mean and SD values for each question. A 1-sample *t* test will be used to determine if the mean satisfaction scores significantly differ from a neutral value. Additionally, a Wilcoxon signed rank test may be used to determine differences in satisfaction levels between using the personalized orthosis and the preexisting orthosis. Any statistically significant variations in user satisfaction between the 2 orthoses will provide insight into the preferential use and comfort of the personalized design.

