## Results

The methodology and approach of this research harbor specific expectations concerning its outcomes. We will use the Qualisys Track Manager from Qualisys to capture biomechanical data with unparalleled accuracy. Once gathered, the data will be processed and analyzed rigorously. With the integration of the Project Automation Framework from Qualisys and Visual 3D from C-Motion, the raw biomechanical data will be transformed into actionable insights that promise to inform and refine orthotic design.

One of the primary quantitative expectations is that the orthosis developed through the new system will either match or surpass the performance of the patient’s current orthosis. This benchmark stems from the belief that the integration of state-of-the-art technology and personalized biomechanical data can achieve superior orthotic design. On the qualitative front, using the QUEST assessment, the expectation leans toward higher satisfaction rates with the new orthosis. Since the orthosis is tailored specifically to the patient’s leg, it is anticipated that its unique design will resonate more with patients, ensuring better fit, comfort, and overall user experience. To ensure comprehensive results, feedback from health care professionals and participants will be actively sought throughout the trial phases. This blend of qualitative and quantitative data aims to present a holistic perspective on the impact of the new orthotic design, setting the stage for potential breakthroughs in patient-centered orthotic solutions. In summary, while this research protocol lays out the groundwork and anticipated outcomes, the subsequent study will seek to not just present numbers but to demonstrate the tangible and intangible benefits of a personalized orthotic approach.

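### In hemiparetic gait, one limb's step, stance and swing values have no better direction on their own, so the planned difference tests cannot by themselves show gait that is as good or better

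*Protocol article*

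**What the plan says.** The relevant statements are spread over five parts of the protocol article.

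- **Variables** (Clinical Outcomes): "temporal-spatial parameters, which capture walking speed, gait cycle duration, step length, step time, time in stance, and time in swing". The recordings are described as "drawing from 10 walking cycles for each leg, and analyzing both kinematics and kinetics".
- **Primary outcomes** (Data Analysis): the defining sentence, which ends by naming the limbs by side rather than by paresis, reads "The primary outcomes will be represented through spatial-temporal data tables and normalized gait graphs, spanning from 0% to 100% of the gait cycle for the".
- **Test** (Data Analysis): "Spatial-temporal parameters will undergo statistical comparisons using paired *t* tests". Its stated purpose is: "This will discern any significant differences between walking with the personalized orthosis, the preexisting orthosis, and walking barefoot". For the curves, the article says that with SPM1D "it becomes feasible to pinpoint regions in the gait cycle where palpable differences between conditions (existing orthosis, personalized orthosis, and barefoot) arise".
- **Population** (Eligibility Criteria and Recruitment Procedures): stroke survivors "who exhibit equinovarus foot secondary to hemiparesis, affecting either the left or right side".
- **Intended conclusion**: Study Design declares noninferiority for the biomechanical outcomes and aims for performance no worse than that of off-the-shelf devices. Results expects that "the orthosis developed through the new system will either match or surpass the performance of the patient’s current orthosis".

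The article gives no better or worse direction for any spatial-temporal variable, no symmetry ratio or difference, and no coding of limbs as paretic and non-paretic.

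**The concern.** Noninferiority, and matching or surpassing a comparator, have meaning only once it is settled which way is worse. Walking speed has a natural direction. Step length, step time, stance time and swing time in one limb of a hemiparetic patient do not: a longer paretic step may bring the limbs closer together or push them further apart. The stated test looks only for a difference between conditions, so it supplies no direction either.

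At stake is what the primary result means. The outputs can show that gait differs between the two orthoses. Without a direction fixed beforehand, which differences count as advantages would have to be decided once the results are known.

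Limb labelling adds to this. With either side affected, a left-leg column mixes paretic and non-paretic limbs.

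**Working it through.** The article gives no mean, SD, sample size or margin for any gait variable, so there is no figure of the plan to reproduce. All values below are assumptions, used only to show what the stated test can and cannot separate.

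**1. The same change from two starting points.** The paretic step lengthens by 0.04 m and the non-paretic step does not change.

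| | Case A | Case B |
|---|---|---|
| Paretic step, old → new (m) | 0.40 → 0.44 | 0.34 → 0.38 |
| Non-paretic step (m) | 0.34 | 0.40 |
| Between-limb difference (m) | 0.06 → 0.10 | 0.06 → 0.02 |
| Paretic/non-paretic ratio | 1.18 → 1.29 | 0.85 → 0.95 |
| Absolute log ratio | 0.163 → 0.258 | 0.163 → 0.051 |
| Sum of the two steps (m) | 0.74 → 0.78 | 0.74 → 0.78 |

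Asymmetry grows in A and shrinks in B. The change in each limb, and in the sum of the two steps, is identical.

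**2. What the paired t test sees.** It uses only the within-patient change: t = mean change / (SD of change / √n). With an assumed SD of change of 0.05 m and n = 20, t = 0.04 / (0.05/√20) = 3.58, against a two-sided 5% critical value of 2.09 on 19 degrees of freedom. The starting values do not enter. In 20,000 simulated trials per case, the test was significant for a longer paretic step in 92.4% (A) and 92.5% (B). As a check, the standardized change is 0.04/0.05 = 0.8, for which an exact calculation gives n = 19 for 90% power, consistent with about 92% at n = 20.

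**3. Would the table of means reveal it?** Not reliably. If half the patients follow A and half follow B, the old-orthosis means are (0.40 + 0.34)/2 = 0.37 m for both limbs, which looks symmetric although every patient has a 0.06 m difference. The new means are 0.41 and 0.37 m. Half the patients moved 0.04 m towards symmetry and half 0.04 m away, and neither the table nor the test shows this.

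**4. Left/right labels.** Suppose the orthosis changes the paretic step by +0.05 m and the other by −0.05 m, and a share s of patients is left-paretic. The mean left-leg change is 0.05s − 0.05(1 − s): −0.02, 0.00 and +0.02 m for s = 0.3, 0.5 and 0.7. If the left/right labels carry into the tests, the sign of the result depends on the case mix.

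**5. A caveat on step 1.** The differences there are between typical values. In the simulation, with independent scatter of 0.05 m in each limb's change, the patients' average absolute difference rose in all significant trials in A, but also in 40% of those in B, because scatter alone inflates an absolute difference. This bears on how a symmetry score is computed (see the fix), not on step 2.

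**The case against.** The strongest reply is that this is an argument from absence. A journal article condenses; ratios, limb coding and direction of benefit may stand in a full protocol or analysis plan that is not shown. That is possible. But the article itself fixes the primary outcomes, a test for any difference and a directional conclusion, and as written these do not fit together. What counts as better is part of the meaning of a primary outcome.

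Some stronger readings are tempting, and the document does not support them:

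- **That every significant difference will be called surpassing.** No section says so. The sentence in Results is an expectation, not a decision rule, and Study Design calls this a feasibility study in which patient feedback and clinical observation chiefly indicate success. The article merely has no rule that prevents that reading.
- **That the t tests are run strictly limb by limb, in absolute units.** This is inferred. The left/right wording describes the tables and graphs, and no units are given for stance and swing.
- **That times must shorten whenever speed rises.** Speed can rise through longer steps at an unchanged cycle time.
- **That SPM cannot show direction.** Its t curve is signed, and the Introduction describes equinovarus as a plantarflexed, inverted foot, so a corrective direction for the ankle curves can be derived. The article does not state one as a criterion.

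The objection also bears on the choice of remedy. Distance of a ratio from 1 treats mirror images differently: steps of 0.48/0.40 m score 0.20 and 0.40/0.48 m score 0.17, whereas the absolute log ratio is 0.182 for both. Symmetry alone would reward shortening the longer step: in Case A, cutting the paretic step from 0.40 to 0.36 m reduces the difference to 0.02 m, but the two steps together fall from 0.74 to 0.70 m. Reducing the curves to a few features would defeat the stated reason for whole-cycle SPM. These points stand and shape the fix.

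**Conclusion.** The point holds for step length, step time, stance time and swing time; it does not extend to walking speed. As the article stands, a significant difference in one of these variables does not by itself show that gait with the new orthosis is better or as good. The size cannot be stated in the trial's own units, because no means or SDs are given. With the assumed values, one and the same test result goes with a between-limb difference that grows by 0.04 m or shrinks by 0.04 m. That the test ignores the starting difference does not depend on those values.

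The conclusion rests on two assumptions: that between-limb balance matters in judging hemiparetic gait, which the article does not discuss, and that no unseen analysis plan already supplies directions and coding. It is a change the sponsor should make, not evidence that the trial will report harm as benefit.

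**What to change.** 1. Code limbs as paretic and non-paretic in all tables, graphs and tests.
2. Base any claim that the new orthosis equals or beats the current one on pre-specified measures with a stated direction:
   - walking speed (higher is better);
   - between-limb symmetry of step length, stance and swing, as the absolute log of the paretic/non-paretic ratio (lower is better), always read together with speed.
3. Compute each ratio per patient from the mean over the cycles, with the same number of cycles in every condition, so that scatter inflates the score equally.
4. Also give stance and swing as a percentage of the cycle.
5. Keep the whole-cycle SPM analysis, but state beforehand the corrective direction for the paretic ankle dorsiflexion and inversion curves, in line with the Introduction's description of equinovarus.
6. Report all other differences as descriptive.

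The cost is some protocol wording and a few derived variables. The 10 cycles per leg already planned are enough to compute them, so no new measurements or patients are needed. The small downside is that benefit can be claimed on fewer variables.

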### Data Analysis

The forthcoming data analysis is designed to provide an in-depth understanding of the impact of personalized orthoses on gait parameters in relation to both preexisting orthosis and barefoot walking. The sample size was estimated at a prespecified power of 90%, while the α value was set at <.05. The primary outcomes will be represented through spatial-temporal data tables and normalized gait graphs, spanning from 0% to 100% of the gait cycle for the left and right legs.

Spatial-temporal parameters will undergo statistical comparisons using paired *t* tests. This will discern any significant differences between walking with the personalized orthosis, the preexisting orthosis, and walking barefoot. Significant distinctions will be recognized based on *P* values, with a threshold set at 95% indicating statistical significance.

Graphical comparisons of kinematic and kinetic data will use the Statistical Parametric Mapping (SPM) method. SPM is tailored for the analysis of 1D biomechanical data series, such as kinematic curves, yielding a nuanced understanding of differences across the entire gait cycle rather than mere isolated time points. The analysis will leverage the *SPM1D* script. By using SPM1D, it becomes feasible to pinpoint regions in the gait cycle where palpable differences between conditions (existing orthosis, personalized orthosis, and barefoot) arise. This rigorous method offers a continuous evaluation over the entire time or space continuum, safeguarding against missing subtle yet clinically pivotal variations.

Simultaneously, the QUEST responses will be statistically analyzed to evaluate patient satisfaction. Scores from the QUEST, which range from 1 (not satisfied) to 5 (very satisfied), will be presented as mean and SD values for each question. A 1-sample *t* test will be used to determine if the mean satisfaction scores significantly differ from a neutral value. Additionally, a Wilcoxon signed rank test may be used to determine differences in satisfaction levels between using the personalized orthosis and the preexisting orthosis. Any statistically significant variations in user satisfaction between the 2 orthoses will provide insight into the preferential use and comfort of the personalized design.

In essence, this multifaceted statistical approach aims to quantify not only the possible biomechanical advantages of personalized orthoses over standard ones but also the subjective satisfaction of users, ensuring a holistic assessment of the new system’s efficacy.

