## Methods

### Study Design

This nonrandomized feasibility study aims to harness advanced scanning technologies and innovative software for the design and refinement of orthotics tailored specifically to the unique anatomical and biomechanical needs of survivors of stroke presenting with equinovarus deformity. Following a noninferiority trial design for biomechanical outcomes and a superiority trial design for qualitative outcomes, our methodology focuses on the development of a novel AFO system. The goal is to ensure its biomechanical performance is at least as effective as off-the-shelf AFOs while also enhancing patient satisfaction. Feedback from patients and clinical observations will serve as the primary indicators of success.

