While contrasting the biomechanics of barefoot walking with orthotic-assisted gait yields valuable insights, our central focus is on the differences between traditionally designed orthoses and those created using the novel system. Contemporary research reinforces the merits of tailored medical interventions, suggesting that custom orthoses can lead to enhanced foot function, pain relief, and overall improved mobility [30,31]. For patients, the benefits of this approach are substantial. Custom-made orthoses, derived from comprehensive biomechanical analyses, not only promise greater comfort but also accelerate gait rehabilitation and minimize complications arising from poorly fitted orthoses [6,7,25]. Such initiatives are in tune with the broader shift in health care toward patient-centered treatments, ensuring holistic and efficacious therapeutic outcomes [32].

Nonetheless, potential limitations exist. While the novel system promises tailored orthoses, individual patient responses, adaptation periods, and unique rehabilitation timelines could present challenges. The variability in individual reactions to orthoses, both in terms of comfort and therapeutic outcomes, remains a critical factor to consider.

This proposed research protocol marks a pivotal juncture between technology and biomechanics in the health care landscape. It signals a shift in orthotic design, embracing recent advancements and a nuanced understanding of biomechanics. The endeavors are not merely about gait rehabilitation recovery but also about setting a new benchmark for precision and efficacy in patient care.

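### Study Design and Data Analysis describe the primary criterion differently, and the biomechanical primary set is unranked across parameters, legs and contrasts

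*Protocol article*

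**What the plan says.** All references are to the protocol article.

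- **Study Design** declares a noninferiority design for biomechanics and a superiority design for the qualitative outcomes. It then states: "Feedback from patients and clinical observations will serve as the primary indicators of success".
- **Data Analysis** states: "The primary outcomes will be represented through spatial-temporal data tables and normalized gait graphs", covering the full gait cycle for both legs. Spatial-temporal parameters are compared by paired t tests across personalized orthosis, existing orthosis and barefoot, "with a threshold set at 95% indicating statistical significance" (P<.05 in the Abstract). Kinematic and kinetic curves are compared by Statistical Parametric Mapping (SPM). The same section says: "The sample size was estimated at a prespecified power of 90%, while the α value was set at <.05".
- **Clinical Outcomes** lists the measures. The spatial-temporal ones are "walking speed, gait cycle duration, step length, step time, time in stance, and time in swing". The kinematic ones include "pelvic movements such as anterior tilt, up obliquity, and internal rotation", then "Hip parameters include flexion, adduction, and internal rotation, while knee parameters assess flexion, varus, and internal rotation", and four ankle and foot angles. The kinetic ones are two moments at each of hip, knee and ankle, plus the vertical ground reaction force.
- **Discussion** says that "our central focus is on the differences between traditionally designed orthoses and those created using the novel system".

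No section names a single parameter, leg or contrast as the one that decides the biomechanical question.

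**The concern.** A reader cannot tell from the article which result decides success. If satisfaction rises and gait is unclear, the Study Design sentence points one way and the Data Analysis sentence may point another. The two sections also treat satisfaction differently. Study Design makes patient feedback a primary indicator, while Data Analysis only allows that the between-orthosis QUEST comparison may be done (the Abstract says that it will be).

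Within Data Analysis, everything measured in the gait laboratory is primary, and any result past the threshold is to be recognized as significant. With a set that wide and no ranking, the parameter, leg or contrast that carries the conclusion can be picked after the data are seen, and one isolated significant result is hard to interpret. The 90% power figure has the same difficulty, because power belongs to a defined endpoint and contrast and the stated primary set singles out neither.

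**Working it through.** The article states no number of tests, so there is no figure to reproduce. The count below is derived from its lists.

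**Parameters (Clinical Outcomes)**
- Spatial-temporal: 6.
- Kinematic: pelvis 3 + hip 3 + knee 3 + ankle and foot 4 = 13.
- Kinetic: 2 + 2 + 2 + 1 = 7.
- Total: 6 + 13 + 7 = 26.

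**Legs and contrasts (Data Analysis)**
- Two legs. Taking walking speed and gait cycle duration once per person and the other four spatial-temporal parameters per leg (an assumption) gives 2 + 4 × 2 = 10 spatial-temporal endpoints. Curves give 20 × 2 = 40.
- Three conditions give up to three pairwise contrasts.

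**Tests with an explicit 5% threshold (spatial-temporal)**

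Chance of at least one false positive among m independent tests with no true difference: 1 − 0.95^m.

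| Reading | m | Chance | Expected false positives (0.05m) |
|---|---|---|---|
| Central contrast, each parameter once | 6 | 26% | 0.3 |
| Central contrast, four parameters per leg | 10 | 40% | 0.5 |
| Three contrasts, each parameter once | 18 | 60% | 0.9 |
| Three contrasts, four parameters per leg | 30 | 79% | 1.5 |

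**Adding the curves, if each is tested at 5% (inferred)**
- (10 + 40) × 3 = 150 tests, or 26 × 2 × 3 = 156 if every parameter is counted per leg.
- 1 − 0.95^150 = 99.95% under independence, with 150 × 0.05 = 7.5 false positives expected.
- Central contrast only: 50 tests, 1 − 0.95^50 = 92%.

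**Effect of correlation**

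Gait parameters are correlated, and the three contrasts share data. Paired t tests were simulated with no true difference and a common correlation rho between endpoints (3,000 runs per setting). Because the article gives no sample size, n = 10, 20 and 30 were assumed; ranges are across n. Each curve is represented by one test at 5%.

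| rho | 150 tests | 50 tests, central contrast | 30 spatial-temporal tests |
|---|---|---|---|
| 0.3 | 99% | 80–81% | 66–69% |
| 0.5 | 91–94% | 64–66% | 56–63% |
| 0.7 | 71–78% | 41–46% | 45–47% |
| 0.9 | 41–44% | 19–22% | 30–31% |

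Correlation lowers the chance of at least one false positive but not the expected number.

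**What ranking achieves**

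One named parameter on one contrast is one test at 5%. Keeping all 150 primary under Bonferroni would need 0.05/150 = 0.00033 per test.

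**The case against.** Four objections carry weight.

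1. *The two statements need not conflict outright.* A reader might infer rival primaries that cannot both decide success. The article does not support that. Study Design sets a joint goal, biomechanics at least as good and satisfaction better, and the Results section repeats the pairing. Clinical observations could also be read to include the gait measurements. This stands: the fault is that the sentences are not reconciled, not that the two domains are incompatible.

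2. *About 150 tests at 5% each, with a false positive almost certain, is not in the text.* The threshold appears with the spatial-temporal tests. No level is given for individual curves, which account for 40 × 3 = 120 of the 150, and SPM already controls error along each curve (though not across curves, legs or contrasts). The opening of Data Analysis can be read as two contrasts rather than three. Near-certainty also needs independence and no true difference anywhere, including between orthosis and barefoot. All of this stands.

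3. *Tests of difference do not give the error rate of the success claim.* Biomechanical success is declared as noninferiority. A chance P<.05 does not establish it, and under no true difference about half of such results would go against the new device. This stands too, so the percentages measure how loosely the primary set is defined, not the risk of a false claim of noninferiority.

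4. *Multiplicity methods usually belong in an analysis plan, and this is a condensed article on a feasibility study.* It cannot be inferred that no adjustment exists. But an analysis plan that adds an adjustment does not make two published sentences about the primary criterion agree. The feasibility label sits beside declared noninferiority and superiority aims and a 90% power statement, so the article does intend comparative conclusions.

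**Conclusion.** The point holds in a limited form. Study Design and Data Analysis describe the primary criterion differently, and the Data Analysis set is unranked across 26 parameters, two legs and up to three contrasts, despite the single central contrast in the Discussion.

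The firm size is for spatial-temporal tests: 26% to 40% on the central contrast and up to 79% over three contrasts, assuming independence and no true difference. Including the curves makes a chance finding very likely at moderate correlation (91% to 99% at rho 0.3 to 0.5) but only 41% to 44% at rho 0.9. That part rests on an inferred 5% level per curve and an assumed sample size.

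This should be fixed, but it does not invalidate the design. The two domains can be combined, and the remedy is wording.

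**What to change.** - Name one biomechanical primary parameter for personalized versus existing orthosis. Walking speed is one option, and it avoids choosing a leg. Test it for noninferiority against a prespecified, justified margin, as Study Design declares, and state whether the 5% level is one- or two-sided.
- Name one QUEST summary score for the same contrast, tested for superiority, as a planned rather than optional comparison.
- State that both must be met, or test them in a fixed sequence. Either way, neither test needs a split alpha.
- Rewrite the primary sentences in Study Design and Data Analysis to match, for example: *Success requires that the personalized orthosis is noninferior to the existing orthosis on the named gait parameter, within the stated margin, and superior on the named QUEST score.*
- Make the barefoot contrasts, the other parameters and the SPM curves secondary or exploratory. Any multiplicity method for them can be left to the analysis plan.

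The cost is a change of wording and fewer results that can be claimed as confirmatory. Requiring both also costs power: if each test had 90% power and the two were independent, the joint power would be 0.90 × 0.90 = 81%, so the sample size basis should be checked against the chosen rule.
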